**Figure 5 F5:**
[figure not shown]
A schematic Stabilogram-Diffusion plot indicating the parameters that can be extracted to describe properties of the postural control process.

C_T _Critical Time, separates short-term and long-term regions. Indicates where the balance control system switches from an open-loop to a closed loop behavior.

C_D _Critical Displacement, indicates mean square displacement of the COP at the Critical Time. Indicator of short-term body sway that the subject is able to control.

D_S _Short-term diffusion coefficient, indicates the stochastic activity (frequency and amplitude) of the COP, the random walker, in the short-term region. Assessed from the slope of the stabilogram-diffusion plot in the short-term region.

D_L _Long-term diffusion coefficient, as D_S _for the long-term region.

H_S _Short-term scaling exponent, indicates the degree of correlation between past and future values of the COP. A value of 0.5 indicates a classical random walk (50% chance of COP displacement in one direction or the other); <0.5 indicates anti-persistence, i.e., the COP tends to come back to a certain equilibrium point (suggests closed-loop control); >0.5 indicates persistence, i.e., the COP tends to drift away (suggests open-loop control). Values can be between 0 and 1.

H_L _Long-term scaling exponent, as H_S _for the long-term region.

Stabilogram-diffusion parameters will be extracted for both eyes-open and eyes-closed conditions. The difference in critical displacement between eyes-open and eyes-closed will be used as an indicator of how much an individual relies on vision to control body sway. A large increase in sway with eyes closed would indicate visual reliance.

3. Berg Balance Scale[82]: The participant is scored on 14 tasks graded on a 0–4 scale to evaluate balance function under different conditions (maximum score 56). Wang et al. [83] found good internal consistency reliability (Cronbach's alpha = 0.77), good inter-rater reliability (ICC(2,1) = 0.87), and moderate correlation with the TUG and usual gait speed (Spearman's rho = -0.53 and 0.46, respectively).

4. Get-Up-and-Go Test[84]: The participant is seated in a chair that is placed 3 meters from a wall. The participant is instructed to rise from the chair, walk at a normal pace to the wall, turn around, return to the chair, and sit down. This task is timed by the researcher using a stopwatch. A practice trial is allowed prior to the actual test. The tester remains near the participant throughout the test to prevent a fall or injury. The TUG [84] was found to be correlated with other measurements, such as gait speed (*r *= -0.61) and the Barthel Index (*r *= -0.78). The TUG was shown to have a sensitivity and specificity of 87% for identifying older adults who are prone to falls. The measures showed significant inter-correlation (r = 0.93). Intra-tester and inter-tester reliability have been reported as high in elderly populations, ICC = 0.92–0.96 [85].

#### Questionnaires

The following questionnaires will be administered to all participants enrolled in the study. Other secondary outcome measures will be analyzed to evaluate whether the training had any benefits extending beyond effects on balance reactions

1. Fear of falling (Fall Efficacy Scale, FES).

2. Memory and cognition (Folstein Mini-Mental State Examination).

3. Late Life Function and Disability Index (LL-FDI). The LL-FDI is a scale developed by Jette and Haley at Boston University. This scale is specifically designed to be sensitive to changes in physical function, something previous measures did not do as well [86,87]. The LL-FDI was recently translated to Hebrew. The function component of LL-FDI found to be a reliable (ICC(2,1) = 0.77–0.90) and valid measure of balance function (Berg Balance Scale, *r *= 0.48, *P *< 0.001) and gait speed (Get-Up-and-Go Test, *r *= -0.52, *P *< 0.001) [88].

### Randomized Cross-Over Clinical Trial

We have decided to conduct a Randomized Cross-Over Clinical Trial, a prospective, analytical, experimental study. Individuals will be randomly allocated to one of two groups (water-based balance training program and controls) and, after a 3-month training period with a 1-month washout period, participants will be switched to the other group for the same period. The control group will not receive any instructions and will not be encouraged to change their physical activity, activities of daily living or social habits during the study. The participants will be examined during the baseline and post-test in a single blind fashion to determine whether a water-based training program that includes external perturbation exercises is an effective treatment to improve speed of stepping and balance control measures in upright stance.

### Statistical analysis

Normality will be ascertained by the Shapiro-Wilk statistic (non-significant) and normal Q-Q plots, indicating that parametric statistics are able to be used. A repeated measures analysis of variance for intervention * time will performed to determine if there are any differences in effect between the two exercise training circuits. The repeated measures of time are baseline, 3 months (post-intervention of the first group – 1^st ^circuit) and (6 months post-intervention of the second group – 2^nd ^circuit). The effects of training on the mean step reaction times (step initiation, time to foot-off, time to foot-contact, preparatory phase, and swing phase), postural stability measure (C_T_, C_D_, D_S_, D_L_, H_S_, H_L_), BBS, TUG, and LL-FDI scores will be calculated using SPSS (version 10.1, SPSS Corp., Chicago, IL). Order of intervention will be also analyzed as a covariate in order to detect any carryover effect from the previous intervention. If a difference between the two training circuits will be found for any variable, *post hoc *comparisons with Bonferroni adjustment will be made. Wilcoxon signed rank test and Mann-Whitney U-tests will be used in case the variable was not normally distributed. Results will be presented as mean values ± SD, the level considered to be statistically significant was *p *< 0.05.

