**Methods/Design:**

The proposed water-based training program involves use of unpredictable, multi-directional perturbations in a group setting to evoke compensatory and volitional stepping responses. Perturbations are made by pushing slightly the subjects and by water turbulence, in 24 training sessions conducted over 12 weeks. Concurrent cognitive tasks during movement tasks are included. Principles of physical training and exercise including awareness, continuity, motivation, overload, periodicity, progression and specificity were used in the development of this novel program. Specific goals are to increase the speed of stepping responses and improve the postural control mechanism and physical functioning. A prospective, randomized, cross-over trial with concealed allocation, assessor blinding and intention-to-treat analysis will be performed to evaluate the efficacy of the water-based training program. A total of 36 community-dwelling adults (age 65–88) with no recent history of instability or falling will be assigned to either the perturbation-based training or a control group (no training). Voluntary step reaction times and postural stability using stabiliogram diffusion analysis will be tested before and after the 12 weeks of training.

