### Sample size estimate

A sample size requirement of 36 was estimated to detect an effect size of 0.8, powered at 80% and alpha of 5% was chosen for a clinically meaningful estimate. The estimation was performed two-sided. Based on a paper by Melzer et al. [53] the investigators found that step execution (average foot-contact times) during the execution of cognitive tasks were 1414 ms ± 417 for elderly fallers and 1165 ± 352 in elderly non-fallers. It was estimated that 32 subjects are required to detect a clinical change in this parameter. For the current study we have used an attrition rate of 10% (32 × 1.10 = 36).

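### The article promises an intention-to-treat analysis, but the three-visit repeated-measures ANOVA it names uses, by default, only participants with all three values

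*Protocol article*

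**What the plan says.** Three statements in the protocol article bear on this point.

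- **Abstract, Methods/Design.** "A prospective, randomized, cross-over trial with concealed allocation, assessor blinding and intention-to-treat analysis will be performed". Intention-to-treat is named only here. It is not defined, and the Statistical analysis section does not mention it.
- **Statistical analysis.** "A repeated measures analysis of variance for intervention * time will performed". The levels of the time factor are also fixed: "The repeated measures of time are baseline, 3 months (post-intervention of the first group", followed by a 6-month value after the second group has trained. Order of intervention enters as a covariate to detect carryover. The software is SPSS 10.1, with no procedure or missing-data option named. The fallback is rank-based: "Wilcoxon signed rank test and Mann-Whitney U-tests will be used in case the variable was not normally distributed".
- **Sample size estimate.** "It was estimated that 32 subjects are required to detect a clinical change in this parameter", and then "For the current study we have used an attrition rate of 10% (32 × 1.10 = 36".

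The section on types of data says that the tests are done on all participants, before and after the training period. It does not say whether someone who stops training is still tested.

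**The concern.** A standard repeated-measures ANOVA with time as a within-person factor needs one value per person at each level of time. A person with a gap is removed from the whole model, not only from the visit that was missed. The stated method therefore does not, by itself, deliver the stated analysis property once any visit is missing, and the plan expects losses.

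The structure of the trial makes this more than a matter of wording. Participants must stay through two 3-month periods and a 1-month washout. A comparison of training with no training is already available at 3 months, before the switch. Someone who gave baseline and 3-month data and then missed only the final test would still drop out of that comparison. In a trial of 36, each such loss matters for precision. People who miss visits in a twice-weekly pool programme may also differ from those who attend.

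**Working it through.** **Inputs**

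| Input | Value | Source |
|---|---|---|
| Randomised | 36 | Abstract; Sample size estimate |
| Required before attrition | 32 | Sample size estimate |
| Attrition | 10% | Sample size estimate |
| Values needed per person | 3 (baseline, 3 and 6 months) | Statistical analysis |
| Allocation ratio | not stated; 1:1 assumed, for the power figures only | assumption |

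**Step 1: the plan's attrition step.** 32 × 1.10 = 35.2, which rounds up to 36. Dividing by the retained fraction instead, 32 / 0.9 = 35.6, also gives 36. This step reproduces. How the 32 was obtained is a separate question and does not bear on this point.

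**Step 2: participants left under complete-case deletion.** If 10% is the total loss by the last visit, 36 × (1 − 0.10) = 32.4 remain and 36 − 32.4 = 3.6 are lost, that is, 3 to 4 people. If instead 10% were lost at each of the two post-baseline visits (an assumption; the article does not say which it means), 36 × 0.9² = 29.2 remain, about 29. A total loss of 15% to 25% (also an assumption) leaves 36 × 0.85 = 30.6 down to 36 × 0.75 = 27.

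**Step 3: precision.** The standard error varies with 1/√N. Compared with complete data on all 36:

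- with 32: √(36/32) = 1.06, about 6% wider;
- with 29: √(36/29) = 1.11, about 11% wider.

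These are upper limits on what another analysis could recover, because a person with a missing visit supplies only part of the information.

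**Step 4: the same loss as power, for scale only.** For a simple two-group comparison at the plan's effect size of 0.8, two-sided 5%, power ≈ Φ(0.8 × √(n/2) − 1.96), with n per group:

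- N = 36, n = 18: Φ(2.40 − 1.96) = 67%;
- N = 32, n = 16: Φ(2.26 − 1.96) = 62%;
- N = 29, n = 14.5: Φ(2.15 − 1.96) = 58%.

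This is not the power of the cross-over analysis, which also uses within-person contrasts. It shows only that a few losses are visible at this sample size.

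**Step 5: the passages side by side.** The abstract promises intention-to-treat. The Statistical analysis section names a method that by default keeps complete cases. The sample size section covers attrition only by recruiting more people. Nothing in the article connects the first statement to the second, for example by imputing before the ANOVA or by using incomplete records.

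**The case against.** The strongest reply is that the article never says incomplete participants are dropped. Imputation before the ANOVA would keep all 36, and a condensed article may leave missing-data rules and the definition of the analysis set to a fuller document. That stands against any claim that a completer analysis has been declared, and silence on imputation alone would be no finding. It does not remove the point. The article names a specific method and a specific property, and the method does not give the property without an added rule. An analysis plan that followed the Statistical analysis section literally would inherit the mismatch.

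A second reply is that intention-to-treat may mean only analysis by allocated group. The ANOVA is compatible with that, but keeping people in their assigned group does not bring back those whom the model deletes.

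Third, inflating 32 to 36 is routine under any analysis set, so it does not show an intention to analyse completers. This is correct. It shows only that losses are expected.

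Fourth, the post hoc comparisons and the rank tests do not inherently need all three visits. This is also correct. The deletion concerns the main repeated-measures model.

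A reader might go further and infer that the result would be biased in favour of training, by an amount that could be worked out from assumed losses in the trained group. The documents do not support that. This is a cross-over, so the group that starts as control also goes through the pool programme, and selective loss can act in both sequences. Nor does the article say that people who stop training go untested.

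**Conclusion.** The point holds as a mismatch between a stated property and a stated method. By default the named ANOVA uses only participants with all three values. At the plan's own 10% attrition, about 3 to 4 of 36 randomised participants would leave the main analysis. About 7 would leave (36 − 29) if the 10% applied at each post-baseline visit, which is an assumption.

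The established consequence is some loss of precision, at most about 6% in the standard error at the stated attrition. Bias is possible, but its direction and size are not established.

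The conclusion rests on the ANOVA being run in its standard form, with no imputation beforehand. The article neither states nor rules out such a step, so the deletion is a default and not a declared exclusion. The change is worth making before analysis, but the mismatch does not by itself invalidate the trial.

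**What to change.** In the Statistical analysis section, replace the repeated-measures ANOVA with a linear mixed model:

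- all available visits of all randomised participants, analysed by assigned sequence;
- fixed effects for visit or period, treatment and order, keeping the carryover term that the section already plans;
- a small-sample degrees-of-freedom correction such as Kenward-Roger.

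State that participants who stop training are still tested at the planned visits and are included. This part matters in its own right. Someone lost before the 3-month test gives the model only a baseline value, and a mixed model alone would not recover a lack of benefit in such people. Report the complete-case ANOVA as a sensitivity analysis only. The cross-over comparison can stay as designed; the fix does not require the main contrast to be moved to 3 months.

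The cost is slightly more analysis work, software that fits mixed models (to be checked against the SPSS version named), and an explicit missing-at-random assumption. No visits are added beyond keeping those already planned.

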### Types of data to be obtained and measurement techniques

The following tests will be performed, for research purposes only, on all participants in the study. All outcome measures will be assessed before and after the training period.

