#### Functional and objective balance tests

The following standardized functional tests will be administered.

1. Voluntary Step Execution Test[53,66,72]: This test will be performed on the portable Kistler 9287 force plate (Kistler Instrument Corp, Winterthur, Switzerland). Participants will be instructed to stand relaxed, view a target placed on a wall 3 m in front of them and to take a step as quickly as possible following a random somatosensory cue. Following a brief learning period, assessments will be made in three directions in random order (forward, backward, and sideways). The time from lifting of the foot (step start) to placing it on the ground will be measured using a portable force plate. The average of these measurements will represent the step execution time. Step execution will also be measured during performance of a secondary attention-demanding task, as described in details by Melzer and Oddsson [53,66,72] (Figure 4). Inter- and intra-rater reliability was good to excellent for the pooled population of young and elderly and for elderly only ((ICC(2,1) = 0.74–0.92 and 0.62–0.88, respectively) [72].

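### The first-period (baseline to 3 months) comparison is not adjusted for baseline, which gives up some precision at low to moderate pre-post correlation

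*Protocol article*

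**What the plan says.** The Statistical analysis section of the protocol article states that "A repeated measures analysis of variance for intervention * time will performed to determine if there are any differences in effect" between the two training circuits. It then lists the levels of the time factor: "The repeated measures of time are baseline, 3 months (post-intervention of the first group", followed by 6 months for the second group. One covariate is named: "Order of intervention will be also analyzed as a covariate in order to detect any carryover effect from the previous intervention". Baseline is therefore one of the repeated outcomes and not an adjustment variable.

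The data needed for adjustment will exist, because the section on types of data says "All outcome measures will be assessed before and after the training period". The design is a two-period cross-over: "after a 3-month training period with a 1-month washout period, participants will be switched to the other group for the same period". The sample size section gives the planning values: "A sample size requirement of 36 was estimated to detect an effect size of 0.8, powered at 80% and alpha of 5" per cent, two-sided, with 32 participants needed before an allowance for attrition.

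**The concern.** Between baseline and 3 months the trial is a randomised parallel comparison of trained and untrained participants. If the effect of 12 weeks of training outlasts a 1-month washout, this is the comparison that carryover cannot touch. The article treats persistence as a live possibility: it plans a carryover check, and its Discussion looks ahead to training benefits being maintained.

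In that comparison an intervention-by-time interaction gives the baseline value a fixed coefficient of 1. ANCOVA estimates the coefficient, and under the usual assumptions its variance is lower whenever the pre-post correlation is below 1, apart from the cost of estimating the slope. With about 32 completers, the difference can matter.

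A fixed coefficient of 1 also over-corrects a chance baseline difference. If the arms happen to differ by δ at baseline, the change-score contrast shifts by (rho − 1)δ. With 16 per arm the standard error of δ is √(2/16) = 0.354σ, so at rho 0.5 an imbalance of one standard error moves the contrast by 0.5 × 0.354 = 0.18σ, against a planned effect of 0.8σ.

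**Working it through.** **Inputs.** Effect size 0.8, two-sided 5% and 32 evaluable participants come from the Sample size estimate section. Equal arms of 16 are assumed; the article does not state a 1:1 ratio. Equal SD σ at each visit is assumed. The 3-month pre-post correlation rho is not given. The nearest figure is the reliability of the step test, "for elderly only ((ICC(2,1) = 0.74–0.92 and 0.62–0.88, respectively", in which 0.62–0.88 is the range for elderly people. That is rater reliability for one test, so it is an optimistic guide at best. I use 0.62 and 0.88 from it, with 0.5 as a cautious value and 0.7 in between.

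**The plan's own figure.** The stated 32 does not follow from an effect size of 0.8 in two parallel groups: 2(1.96 + 0.842)²/0.8² = 24.5, so 25 per arm or 50 in total. A paired calculation gives 13 (15 with the t distribution). The figure 32 appears only as a per-arm number using 249 ms and SD 352. That is a separate matter; 32 is used here only as the planned number of completers.

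**First-period variances per person.**
- Change score: 2(1 − rho)σ², with 30 residual df.
- ANCOVA: (1 − rho²)σ², with 29 residual df.
- Ratio: (1 − rho²)/[2(1 − rho)] = (1 + rho)/2.
- Estimating the slope inflates the ANCOVA variance on average by about 1 + 1/28 = 1.036.

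**Power** is from the non-central t distribution with non-centrality 0.8/√(2v/16), where v is the variance factor. At rho 0.5, change scores have v = 1.00 and non-centrality 0.8/0.354 = 2.26, giving 59%. ANCOVA has v = 0.75 and non-centrality 0.8/0.306 = 2.61, giving 71%, or 70% with the slope allowance.

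**The planned three-level test.** If training effects persist fully, the difference between sequences at baseline, 3 and 6 months is (0, d, 0). The 2-df interaction then has non-centrality (16/2)(2/3)d²/(1 − rho) on 2 and 60 df, assuming equal correlations. At rho 0.5 this is 6.83.

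| rho | Variance ratio | Change score | ANCOVA | ANCOVA, slope allowance | Planned 2-df test, effects persist |
|---|---|---|---|---|---|
| 0.5 | 0.75 | 59% | 71% | 70% | 62% |
| 0.62 | 0.81 | 71% | 80% | 78% | 75% |
| 0.7 | 0.85 | 81% | 86% | 85% | 85% |
| 0.88 | 0.94 | 99% | over 99% | over 99% | over 99% |

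Allowing for the slope, the variance advantage over change scores ends where 1.036(1 + rho)/2 = 1, at rho of about 0.93.

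**The cross-over contrast.** For the 3- versus 6-month difference within person, the covariance with the single baseline is proportional to the baseline-to-3-month correlation minus the baseline-to-6-month correlation. If the two are equal, it is zero and adjustment only costs the slope: simulated variance ratio 1.03–1.04. Under an AR(1) pattern the simulated ratio is 0.96–0.99.

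**The case against.** The strongest reply is that the plan specifies a cross-over analysis over three time points, not a two-point change score, so the 59% to 71% comparison prices a test that the article does not name. This largely stands. Against the planned 2-df interaction with persisting effects, the gain at rho 0.5 is from 62% to about 70–71%, and at rho 0.7 it is one or two points at most. If effects wash out fully, the planned test does lose power, but through its 2-df form: at an effect size of 0.4 and rho 0.5 it has 49%, against 59% for a 1-df 3- versus 6-month contrast, with or without baseline as covariate.

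A reader might infer that the loss affects every analysis however the cross-over is settled, and that baseline should be a covariate wherever second-circuit data are used. The article does not support that: each participant is his or her own control in the cross-over contrast, and the common baseline largely cancels. A reader might also infer that baseline is discarded or that the plan is biased. Neither holds. The interaction uses change from baseline, which is more precise than a post-only comparison once rho exceeds 0.5, and change scores are unbiased over randomisation. The shift from imbalance described above is conditional on the sample drawn.

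Finally, the gain will differ by outcome. If the quoted reliabilities are taken as rho, the variance reduction (1 − rho)/2 is 2–4% for the TUG (ICC 0.92–0.96) and 5–12% for the LL-FDI (0.77–0.90), before the slope cost.

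**Conclusion.** The point holds for the first-period between-group comparison only. There the article fixes a valid but less efficient use of a baseline that is already collected. ANCOVA would cut the variance by 25% at rho 0.5, 19% at 0.62 and 6% at 0.88, a little less after the slope is estimated. The power gain over change scores is roughly 11–12 points, 7–9 points and 4–6 points at rho 0.5, 0.62 and 0.7, and negligible near 0.9. These figures rest on an assumed rho, equal arms of 16, equal SDs and the plan's own effect size. Calling the change free of any downside would go too far: it costs a degree of freedom and about 3.6% in variance, and in the cross-over contrast it changes variance by only about +4% to −4%. It is an inexpensive improvement to one comparison, not a fault that invalidates the planned analysis.

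**What to change.** Add to the Statistical analysis section: for each outcome, the 3-month between-group effect will be estimated by ANCOVA with assigned group as factor and the participant's own baseline value as covariate, and reported as an adjusted mean difference with 95% CI. Report it alongside the planned cross-over analysis, and state its role in advance so that the choice between the two does not depend on the carryover result. Do not require the single baseline as a covariate in the 3- versus 6-month within-person contrast.

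The cost is a sentence or two of text, one degree of freedom and the small slope loss. No further measurements or participants are needed.

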Step training (volitional or compensatory) may increase the speed of central neural processing capabilities during the specific function. During the APA phase, neural control of volitional stepping differs from stepping evoked by postural perturbation [52,57], whereas these APAs are typically absent or significantly reduced during large perturbations [52,58,59]. Thus it was suggested that training volitional stepping might lead to improved control of the APAs, but would probably not improve compensatory stepping, especially due to lack of training specificity. Finally, the swing phase incorporates the actual motor execution of the task when the leg is lifted and moved to the target location. Hence, specific and progressive training using water resistance to improve the swing phase speed may provide a benefit in the ability to execute not only effective compensatory stepping reactions but also volitional stepping response.

The present study aims to test a novel water-based training program that includes perturbation of balance during water-based exercises, specifically targeting stepping responses. To date, only a few studies have examined the effects of water-based training on balance control in the elderly. These studies demonstrated increased Berg Balance score [60], improved leaning balance [61,62] and Functional Reach [63], and improvement in the step test (step 7.5 cm high and return to the floor as many times as possible over a period of 15 seconds), quality of life, but not fear of falling [64], following training. To our knowledge, no studies have directly addressed the potential of using perturbation-based training to counter specific impairments in compensatory and voluntary stepping responses. By training in a water environment, the fear of falling as a result of perturbation exercises may be reduced in elderly persons. Fear of falling may reduce the feasibility of land-based perturbation training (i.e., outside the water). We hypothesize that subjects who undergo a water-based training program that includes perturbation exercises will show greater improvements in the ability to step rapidly, compared to control subjects who undergo no training. In this paper, we describe the development of a water-based training program that includes perturbation exercises and lay out the protocol for a randomized controlled cross-over trial to evaluate the efficacy of this program.

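### The stated aim and the post hoc gate compare the two training circuits, not training with no training, and so match neither the hypothesis nor the named model

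*Protocol article*

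**What the plan says.** The hypothesis at the end of the Background is that trained subjects "will show greater improvements in the ability to step rapidly, compared to control subjects who undergo no training". The section on the cross-over design puts the same question: whether the programme "is an effective treatment to improve speed of stepping and balance control measures in upright stance". The design has two sequences: "after a 3-month training period with a 1-month washout period, participants will be switched to the other group for the same period".

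The Statistical analysis section names the model, "A repeated measures analysis of variance for intervention * time will performed", and gives its purpose: "to determine if there are any differences in effect between the two exercise training circuits". It then sets the time points: "The repeated measures of time are baseline, 3 months (post-intervention of the first group", labelled the first circuit) and 6 months, after the second group's training, labelled the second circuit. Bonferroni-adjusted post hoc comparisons follow on a condition: "If a difference between the two training circuits will be found for any variable".

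Two further sentences in that section bear on the point. One says, without any condition, that the effects of training on the listed outcomes will be calculated. The other enters order of intervention as a covariate to detect carryover.

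**The concern.** By the section's own labels, circuit 1 is the first group's training and circuit 2 is the second group's training. A difference between them shows that training worked better in one period or order than in the other. It does not show whether training works, which is the trial's question. The circuit wording appears twice, once as the aim of the test and once as the condition for follow-up comparisons, so it is hard to dismiss as a single slip.

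An analyst who follows the wording could report no difference for a programme that succeeds in both groups, and then make no post hoc comparisons. The same analyst could report a difference when only order or period effects separate the circuits.

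**Working it through.** The plan attaches no figure to this test, so there is none to reproduce. The check asks what each candidate contrast does when the programme works equally well in both circuits.

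**Inputs**
- Three time points and two groups: Statistical analysis section.
- Effect size 0.8 SD, two-sided 5%, 32 subjects before attrition, hence 32 / 2 = 16 per group: Sample size estimate section. Equal groups are assumed.
- Within-person correlation 0.3, 0.6 or 0.8: assumed, because the article gives none.

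**Expected means (baseline, 3 months, 6 months), benefit d in each circuit, full washout**
- Group trained first: (0, d, 0).
- Group trained second: (0, 0, d).

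**What each contrast estimates**
1. Circuit 1 versus circuit 2: (first group, 3 months minus baseline) minus (second group, 6 months minus 3 months) = (d - 0) - (d - 0) = 0, for any d. A 5% test of a contrast that is truly zero rejects 5% of the time.
2. Group by time interaction: the group differences at the three times are 0, d and 0 - d = -d. They are not constant, so the interaction is not null.
3. Cross-over training versus no-training contrast: half of [(first group, 3 months minus 6 months) minus (second group, 3 months minus 6 months)] = [d - (-d)] / 2 = d.

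With complete carryover the first group's means become (0, d, d). The circuit contrast stays at 0, the group differences become 0, d, 0, and the cross-over contrast becomes [0 - (-d)] / 2 = d/2.

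**Simulated rejection rates** (10,000 runs per setting, SD 1, d = 0.8)

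| Scenario | Correlation | Circuit contrast | Group by time interaction | Cross-over contrast |
|---|---|---|---|---|
| Full washout | 0.3 | 5.1% | 92.6% | 95.8% |
| Full washout | 0.6 | 4.6% | 99.6% | 99.9% |
| Full washout | 0.8 | 5.2% | 100% | 100% |
| Complete carryover | 0.3 | 4.9% | 46.6% | 45.5% |
| Complete carryover | 0.6 | 4.9% | 72.6% | 69.2% |
| Complete carryover | 0.8 | 5.0% | 95.6% | 93.0% |

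At d = 0 with full washout, all three tests reject in 4.8% to 5.2% of runs. At d = 0.5 the circuit contrast still rejects in only 4.8% to 5.3%, so it does not respond to the size of the benefit.

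**A 3-month comparison adjusted for baseline, for reference.** The standardised effect is d / sqrt(1 - rho^2), with 16 per group and 29 degrees of freedom. At correlations 0.3, 0.6 and 0.8 it is 0.84, 1.00 and 1.33, and power is about 63%, 78% and 95%. Carryover cannot affect it, because it uses no data after 3 months.

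**The case against.** The strongest reply is that the named model already carries the treatment contrast. With equal benefit in both circuits the intervention by time interaction is clearly non-null, and it retains some power even with complete carryover. If the gate is read as significance of that interaction, followed by post hoc tests in the usual way, it opens in 93% or more of runs with full washout. The condition applies only to the post hoc step, not to the analysis of variance, and the section separately says that training effects will be calculated.

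This stands against a stronger reading. A reader might infer that a programme effective in both circuits would never be tested against no training, or that its chance of detection is 5% without qualification. The document does not support either: the 5% belongs to the literal circuit contrast alone.

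The reply does not rescue the wording. A two-degree-of-freedom interaction over three times does not show at which time or in which direction the groups differ, and the comparisons that would show it sit behind the circuit condition. The sentence on calculating training effects names outcomes and software, but no contrast or test.

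It can also be said that a condensed article leaves contrasts to a fuller plan. That would excuse silence. Here the article states an aim and a condition that conflict with its own hypothesis.

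**Conclusion.** Wrong as written. The stated aim and the post hoc gate address circuit 1 versus circuit 2, the hypothesis addresses training versus no training, and the named model tests something that matches neither statement cleanly. Taken literally, the circuit contrast rejects in about 5% of trials whenever the benefit is equal in both circuits. That follows from the algebra and does not depend on effect size, correlation or carryover.

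The rates for the interaction (93% to 100% with full washout, 47% to 96% with complete carryover) do depend on assumptions: 16 per group, a true effect of 0.8 SD and the assumed correlations. They show that the planned data and model can answer the trial's question. The fault lies in which comparison the text declares to be the test and which it makes conditional.

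**What to change.** Replace the aim and the gate in the Statistical analysis section with wording such as:

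> For each primary outcome, the primary test is the difference between the trained and untrained conditions, estimated from the cross-over data with period and sequence in the model, two-sided at 5% and reported with a 95% confidence interval. It is carried out whatever the comparison of the two circuits shows. The circuit comparison is reported only as a check on order, period and carryover.

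A baseline-adjusted comparison of the groups at 3 months can be added as a sensitivity analysis free of carryover. It should not replace the cross-over contrast without acknowledging the trade-off. If washout is complete it has less power (about 63%, 78% and 95%, against 96%, 99.9% and 100%, at correlations 0.3, 0.6 and 0.8). If carryover is complete the cross-over contrast estimates only half the effect and the 3-month comparison is the safer one.

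The cost is a change of wording. The planned baseline, 3-month and 6-month assessments supply everything needed, so no new data are required.
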